**Fig. 1 Fig1:**
[figure not shown]
Timeline and procedure

**Table 1 Tab1:** Instruments for measuring clinical efficacy and cost-effectiveness

Dimension	Methodology	Assessment measures	Stakeholder	T0	T1	T2
Clinical efficacy						
Psychopathology	Clinical interview	**Minors** (6-18 years old): Kiddie Schedule for Affective Disorders and Schizophrenia-Present and Lifetime version (K-SADS-PL) (DSM-5) **Adults**: Structured Clinical Interview for DSM Disorders (SCID-I)	Patient	x		
Physical and clinical variables	Brief clinical interview	Comorbidities, medication, illness duration, Body Mass Index, among others	Patient	x	x	x
Eating Disorder psychopathology	Questionnaire	- Eating Disorders Examination Questionnaire (EDE-Q) - Short Evaluation of Eating Disorders (SEED)	Patient	x	x	x
Depression	Questionnaire	Beck Depression Inventory-II (BDI-II)	Patient	x	x	x
Anxiety	Questionnaire	State-Trait Anxiety Inventory (STAI)	Patient	x	x	x
Motivation to change	Questionnaire	**Patients with Anorexia Nervosa**: Anorexia Nervosa Stages of Change Questionnaire (ANSOCQ) **Patients with Bulimia Nervosa or Binge Eating Disorder**: Bulimia Nervosa Stages of Change Questionnaire (BNSOCQ)	Patient	x	x	x
Dropout	Telephone interview	Reasons for dropout	Clinician responsible for the online monitoring		x	x
Risk of suicide	Questionnaire	Beck Hopelessness Scale (BHS) / Suicide Intent Scale (SIS)	Patient / Clinician responsible for the online monitoring	x	x	x
Quality of life	Questionnaire	**12-14 years old**: EQ-5D-Y (children version) **> 14 years old**: EQ-5D-5 L	Patient	x	x	x
Caregiving experience	Questionnaire	Experience of Caregiving Inventory (ECI)	Family caregiver	x	x	x
Quality of life	Questionnaire	EQ-5D-5 L	Family caregiver	x	x	x
Cost-utility and cost-effectiveness analysis						
Cost related to the development and maintenance of the online platform	Telephone interview	Staff involved, number of extra hours x pay rate/hour	Technical staff	x	x	
Costs related to healthcare utilization, medication and school and / or work absenteeism	Questionnaire	iMTA questionnaire for Costs associated with Psychiatric Illness (TiC-P) / iMTA questionnaire for Costs associated with Psychiatric Illness, Parent-Form (TiC-P Children)	Adult patient / family caregiver (referring to minor patient)	x	x	x
Patient’s healthcare utilization	Telephone interview	Number of visits to ED specialists, number of visits to the emergency department, medication consumption and its costs	Clinician responsible for the online monitoring	x	x	x
Cost of implementing the online intervention	Telephone interview	Clinicians involved, number of extra hours for online monitoring x pay rate/hour	Clinician responsible for the online monitoring		x	
Usability and satisfaction	Questionnaire	- Client Satisfaction Questionnaire (CSQ-8) - System Usability Scale (SUS)	ED specialists and patients from the experimental group		x	

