### Procedure and randomization

First, all material with information related to the study (research protocol, informed consent, patient information sheet, Data Collection Logbook, safety- and privacy-related issues concerning the TCApp) have been submitted for approval to each one of the Ethical Committees of the participating hospitals. It should be mentioned that the approval of the Ethical Committee of the University leading the study (Open University of Catalonia, UOC) was obtained on February 21st, 2017.

Participants will be recruited after previous recommendation by one of the ED specialists working at each centre. Specialists will do a preliminary screening following the inclusion and exclusion criteria in order to identify potential candidates for the study. Interested individuals will be able to confirm their participation by notifying the ED specialist who will be responsible for their treatment. Then, an information letter and an informed consent form will be delivered to them.

After completing and signing these documents (for underage patients, their parents will be required to sign the informed consent and for patients aged more than 18 years, they will have to sign informed consent themselves), initial clinical interviews will be conducted by psychologists or other collaborators working in the ED unit. All interviewers will be previously trained in administering the K-SADS-PL or SCID interview, depending on the participant’s age. The objective of these interviews is: a) to determine whether participants are definitely eligible for the study following the inclusion criteria, b) to establish the diagnosis for each patient and c) to evaluate them for possible comorbidities. At this time, sociodemographic and clinical data of each patient will also be collected through a brief interview. Then, those who meet the inclusion criteria will be invited to complete the baseline questionnaires for the study. During this baseline evaluation (T0), questionnaires will be administered to patients, their informal caregivers and the ED specialist responsible for the online monitoring of each patient. In addition, telephone interviews will be conducted with the technical staff and the ED specialists.

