After completion of the baseline questionnaires, participants will be randomized to one of the two study conditions (experimental or control group). Randomization will be carried out by an independent researcher in blocks of 10 participants within each ED unit (50% of patients from each block will be assigned to the experimental group and the other 50% to the control group), using a random allocation program. Allocation concealment will be also ensured.

After this, patients will be notified about the group they belong to during their next visit to the ED unit. At this time, patients from the experimental group will be given oral and written instructions about how to download and use the TCApp. ED specialists responsible for the online monitoring will be also taught the basic principles for using the application. In turn, patients from the TAU control group will be told that access to the TCApp will be offered to them after a waiting period of 6 months (T2 evaluation completed).

Then, each group of patients will receive the treatment that corresponds to them during a period of 12 weeks. At the end of the 12-week treatment, patients from the experimental group will stop using the TCApp and the evaluation post-treatment (T1, 12 weeks later) will be carried out, including: a) a brief clinical interview (patients), b) questionnaires (patients, informal caregivers, ED specialists); c) telephone interviews (technical staff, ED specialists) and d) focus groups with ED specialists of each institution who are interested in participating as well as with patients of the experimental group.

In the follow-up evaluation T2, 6 months after the beginning of treatment, patients, their informal caregivers and ED specialists responsible for the online monitoring will complete some questionnaires. In addition, telephone interviews will be conducted with ED specialists and a brief clinical interview will be carried out with patients. At the end of this phase, patients from the control group will be given access to the TCApp after being contacted by the ED specialist who will be responsible for their online monitoring.

Figure 1 presents the procedure and the timeline of the study and Table 1 provides a detailed description of the methodology with a definition of the study variables and their assessment tools.

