### Study conditions

The experimental group will receive the standard treatment based on CBT principles that is offered by the different ED units in Spain, plus an online intervention using the TCApp for a period of 12 weeks. Only one ED specialist will be responsible for the online monitoring of each patient. For the specific purposes of our study, this role has been assigned to the nursing staff for most of the centres.

The TCApp application proposes patients a series of different functionalities, including daily self-records of their thoughts, emotions and actions, a chat with their therapists and motivational exercises. An online platform of the TCApp (BackOffice) is also available for therapists for the online monitoring of each patient. There, therapists have the possibility to follow the patient’s daily self-records, generate personalized reports and graphs and communicate with him/her via chat, based on the information that the patient has provided online.

During these 12 weeks, the patient should use the TCApp at least once a day, completing at least one self-record per day and/or contacting his/her therapist via chat when needed. The therapist responsible for the online monitoring should connect to the online platform and perform the following actions at least once a week: follow the patient’s daily self-records, generate personalized reports or graphs and communicate with him/her via chat. After a 12-week period, patients from the experimental group and their therapists will stop using the TCApp (they will be discharged).

The TAU control group will receive the standard face-to-face CBT, offered by the different ED units in Spain. Patients from the control group will be offered access to the TCApp after a 6-month period.

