### Economic evaluation

A cost-effectiveness analysis of the TCapp will be performed, which will compare the effects and costs of the intensive online intervention (TAU + TCapp) with the ones for TAU. The effects will be measured with quality-adjusted life years (QALYs) obtained from the EQ-5D-5 L and EQ-5D-Y questionnaires. Furthermore, the effects regarding the primary outcome variables (EDE-Q, SEED) will also be taken into account. On the other hand, costs will cover the development of the App, the costs of using the product, and the medical costs (visits and medication) for both groups. Moreover, societal costs such as productivity losses and the caregiving burden will also be assessed. Information on costs will be obtained from the iMTA questionnaire and from interviews with the clinicians and technicians. This evaluation will determine the incremental costs and effects of the intensive intervention compared to the control condition , and will produce an incremental cost-effectiveness ratio (ICER). 

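### Table 1 takes healthcare use and dropout reasons in both arms from the online-monitoring clinician, whose weekly patient contact exists only in the TCApp arm, so ascertainment could differ by arm, chiefly between T0 and T1

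*Protocol article*

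**What the plan says.** All references are to the protocol article.

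- **Table 1, cost rows.** Healthcare utilisation is obtained by telephone interview at T0, T1 and T2 and consists of "Number of visits to ED specialists, number of visits to the emergency department, medication consumption and its costs". The stakeholder column gives only the "Clinician responsible for the online monitoring". The row is not limited to one arm, whereas the usability and satisfaction row does name the experimental group.
- **Table 1, dropout row.** Reasons for dropout, at T1 and T2, come from the same person.
- **Study conditions.** The monitoring clinician of a TCApp patient must review self-records, produce reports or graphs and chat at least weekly for 12 weeks, after which patient and therapist stop using the app. Of the role, the article says that "this role has been assigned to the nursing staff for most of the centres". For controls, "Patients from the control group will be offered access to the TCApp after a 6-month period".
- **Procedure and randomization.** T0 questionnaires go to "the ED specialist responsible for the online monitoring of each patient". Next, "After completion of the baseline questionnaires, participants will be randomized to one of the two study conditions". After T2, controls receive access "after being contacted by the ED specialist who will be responsible for their online monitoring".
- **Secondary outcome measures, clinicians.** The Suicide Intent Scale is listed under the online-monitoring clinicians, but its description assigns completion to the clinician who treats the patient.
- **Economic evaluation.** Costs include "the medical costs (visits and medication) for both groups", with information from the iMTA questionnaire (TiC-P) and from clinician and technician interviews.

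**The concern.** A cost item needed on equal terms in both arms is assigned to an informant defined by a task that belongs to the experimental treatment. If that person knows TCApp patients better than controls, the same question is answered with different completeness in the two arms. Randomisation does not protect against this, because the difference arises in measurement after allocation. Analysis cannot recover events that the informant never knew about.

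Incremental cost is the numerator of the ICER, and the economic evaluation is the second of the three stated objectives. Reasons for dropout would be exposed in the same way, and Table 1 names no second source for them.

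**Working it through.** The plan gives no figure to reproduce, so the check compares passages.

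**1. Who is the informant for a control patient?**

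| Place | What it implies |
|---|---|
| Procedure and randomization, T0 assessment | A monitoring specialist is named for each patient before the arm is known, so later controls have one too |
| Procedure and randomization, after T2 | Responsibility for the online monitoring of controls is put in the future tense |
| Study conditions | Monitoring duties are described for TCApp patients only; nurses hold the role at most centres |
| Secondary outcome measures, Suicide Intent Scale | The monitoring clinician is treated as the treating clinician |
| Sample | Nursing belongs to the team that supports all patients |

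The first row means that an informant probably exists for controls. The rows together do not say whether that informant treats or follows the control patient before T2.

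**2. When does scheduled contact differ?**

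- At T0 there are no arms yet.
- From T0 to T1, TCApp patients have at least 1 contact per week × 12 weeks = at least 12 online contacts. For controls the article describes none in this role.
- From T1 to T2, TCApp patients have stopped and controls have not started, so scheduled online contact is nil in both arms.

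The asymmetry therefore falls mainly on the T1 report.

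**3. Which data are exposed?** The clinician interview is one of two cost sources. The TiC-P (adult patients) or TiC-P Children (caregivers of minors) covers healthcare use and medication at T0, T1 and T2 in both arms. The brief clinical interview also records medication from the patient at all three times. Emergency visits are named only in the clinician interview. The visit types listed for the TiC-P are given as examples, so that questionnaire may cover them as well.

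**4. How large could the effect be?** This needs capture rates, which the article does not give. With equal true use, the ratio of recorded use (TCApp to control) is the capture rate in the TCApp arm divided by that in controls. Assumed values, for illustration only:

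- 0.90/0.90 = 1.00
- 0.90/0.80 = 1.13
- 0.90/0.70 = 1.29
- with the last pair reversed, 0.70/0.90 = 0.78

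In absolute terms, assume v true contacts per patient, full capture in the TCApp arm and a share c captured in controls. The false difference is v(1 − c). For v = 6 it is 0.6 at c = 0.9, 1.2 at c = 0.8 and 2.4 at c = 0.6. For v = 12 these become 1.2, 2.4 and 4.8. The range includes no effect (c = 1), and nothing in the article selects a value or a sign.

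**The case against.** The strongest reply is that the label in Table 1 is only a name for a member of the unit's staff. A monitor appears to be designated for every patient before randomisation. The Suicide Intent Scale text treats this person as the treating clinician, and the same person is listed for that scale at all three times without restriction by arm. Nurses belong to the teams that look after all patients. The Statistical analysis section speaks more broadly of interviews with ED specialists about dropout. No passage says that the informant answers from app contact or memory instead of unit records, and no passage says that the weekly chats convey visit counts. The TiC-P gives a parallel record in both arms, and how overlapping sources are combined is properly left to the analysis plan.

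Most of this stands, and it limits the point. A reader might infer from Table 1 that control cost data will be missing, or that controls will be under-recorded and the TCApp made to look more expensive. The article supports neither inference. The T0 wording argues against missing data, and the direction of any bias would depend on capture rates that nobody has stated.

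The reply does not show that ascertainment is equal. Nothing requires the informant to treat controls or to use records, and the passages on the role do not agree. The TiC-P limits the harm but does not remove it, because the Economic evaluation section draws on the interviews too. The choice of informant is a data-collection decision stated in this article, not a detail left to the analysis plan.

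**Conclusion.** The point holds as a risk, not as an established bias. Clinician-reported utilisation and dropout reasons rest on a role whose scheduled contact exists only in the TCApp arm during the 12-week treatment. The article is not consistent on whether the holder treats or follows controls before T2. Ascertainment could therefore differ by arm, chiefly for T0 to T1, in one of the two cost sources. Size and direction cannot be derived from the document; the ratios above rest wholly on assumed capture rates. The consequence is confined to the economic evaluation and the account of dropout. The EDE-Q comparison is unaffected. The change is still worth making, because it is cheap and removes the doubt before data are collected.

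**What to change.** - In Table 1 and the Qualitative assessment section, name one informant for healthcare utilisation and dropout reasons in both arms: the clinician treating the patient at the unit, answering from the unit's visit and prescription records.
- Keep the online-monitoring clinician as informant only for the extra monitoring hours, which arise only in the TCApp arm before T2.
- Reconcile the T0 and post-T2 wording in Procedure and randomization with the Suicide Intent Scale description, so that it is clear who holds the monitoring role for a control patient and whether that person treats the patient.

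The cost is a wording change, a small amount of record look-up, and a change of interviewee at centres where the monitor is not the treating clinician. Where they are the same person, only the use of records is new. The telephone interviews are already scheduled, so no assessment is added.

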### Study conditions

The experimental group will receive the standard treatment based on CBT principles that is offered by the different ED units in Spain, plus an online intervention using the TCApp for a period of 12 weeks. Only one ED specialist will be responsible for the online monitoring of each patient. For the specific purposes of our study, this role has been assigned to the nursing staff for most of the centres.

The TCApp application proposes patients a series of different functionalities, including daily self-records of their thoughts, emotions and actions, a chat with their therapists and motivational exercises. An online platform of the TCApp (BackOffice) is also available for therapists for the online monitoring of each patient. There, therapists have the possibility to follow the patient’s daily self-records, generate personalized reports and graphs and communicate with him/her via chat, based on the information that the patient has provided online.

During these 12 weeks, the patient should use the TCApp at least once a day, completing at least one self-record per day and/or contacting his/her therapist via chat when needed. The therapist responsible for the online monitoring should connect to the online platform and perform the following actions at least once a week: follow the patient’s daily self-records, generate personalized reports or graphs and communicate with him/her via chat. After a 12-week period, patients from the experimental group and their therapists will stop using the TCApp (they will be discharged).

The TAU control group will receive the standard face-to-face CBT, offered by the different ED units in Spain. Patients from the control group will be offered access to the TCApp after a 6-month period.

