### Sample size calculation

The a priori sample size calculation was based on results from previous studies that implemented Internet-based programs in the treatment of EDs [58–60]. A small between-group effect size (Cohen’ s d = 0.40) is expected. The calculation was conducted by the software program G*POWER. The primary analysis will concern the hypothesis that the average level of eating pathology at post-intervention in the control group, based on the EDE-Q scores, will be higher than the average levels of eating pathology in the experimental group. Assuming an alpha of 0.05 and a power of 0.80 (β − 1) in an independent samples one-way t-test study, a minimum of 100 participants would be required per study arm. Allowing for a dropout rate of 25% of study participants from baseline, a total of 250 participants need to be recruited.

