### Statistical analysis

Both intent-to-treat and completers analyses will be carried out. Intent-to-treat analysis will include every participant who will be randomly allocated to one of the study conditions, that is to say, 250 patients. Whenever possible, we will try to collect follow-up data from participants who have dropped out, in order to keep our dataset as complete as possible. Baseline differences between completers and dropouts will be analysed (Pearson’s chi-square test Student’s t test) using data from the clinical interviews and the baseline questionnaires and possible reasons for dropout will be examined through interviews with the ED specialists (T1, T2).

A participant will be considered a completer if he/she has completed the initial clinical interview as well as T0 and T1 evaluations. For participants from experimental group, to be considered completers they will have to have used the TCApp at least 70% of the time that was initially agreed upon before the start of the experiment (at least once a day during a period of 12 weeks). Only data from completers will be used to determine the treatment effect on the main outcome variable.

All analyses will be carried out using SPSS (Statistical Package for the Social Sciences). First, we will examine the data using descriptive statistics. Between-group analysis will be conducted using Pearson’s chi-square test or Fisher’s exact test for categorical data and Student’s t test or the Mann-Whitney U test for continuous variables, depending on the normality of the distribution. The normality of the distribution of the variable will be assessed using the Kolmogorov-Smirnov test. The effect of the intervention in terms of reduction in the primary and secondary outcome measures over time will be computed by using a mixed model linear regression analysis with time, experimental condition and their interaction as independent variables. Since there may be some heterogeneity in the implementation of the intensive online intervention across the different participating institutions, between-centre heterogeneity will be explored in subgroup analyses.

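### Online monitoring by one clinician per patient nests only the TCApp arm, but the sample size assumes independent patients and the stated model names no monitor or ED-unit term

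*Protocol article*

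**What the plan says.** **Delivery.** Under Study conditions: "Only one ED specialist will be responsible for the online monitoring of each patient". The article adds that "this role has been assigned to the nursing staff for most of the centres". At least weekly for 12 weeks, that clinician reviews the patient's self-records, produces reports or graphs, and communicates by chat. Controls receive face-to-face CBT from the same ED units and are offered the app only after the 6-month assessment.

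**Randomisation** (Procedure and randomization). Patients are randomised individually, in blocks of 10 within each ED unit.

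**Sample size** (Sample size calculation). The basis is Cohen's d of 0.40. The article continues: "Assuming an alpha of 0.05 and a power of 0.80 (β − 1) in an independent samples one-way t-test study". The result is 100 patients in each arm. No ICC or design effect appears.

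**Analysis** (Statistical analysis). The intervention effect comes from a "mixed model linear regression analysis with time, experimental condition and their interaction as independent variables". Random effects are not described. The article expects that implementation of the online intervention may differ between institutions, and its only stated response is to explore centre differences in subgroup analyses.

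The number of monitors, patients per monitor and any ICC are not given.

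**The concern.** The monitor delivers part of the experimental treatment. Patients who share a monitor share that clinician's skill and engagement with the app, so their outcomes may be correlated. Before T2 this source of correlation exists in the TCApp arm only, so it does not cancel between the arms.

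If it is ignored, the standard error of the treatment effect can be too small, the false-positive rate can exceed 5%, and a valid test can have less than the stated power. Part of an apparent app effect could also reflect a few particularly engaged monitors. The same reasoning applies to the other patient-level outcomes.

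Subgroup analyses by centre describe where the effect differs. They leave the standard error of the overall effect unchanged.

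**Working it through.** **1. The plan's own figure.** With d = 0.40, two-sided alpha 0.05 and power 0.80, the exact independent-samples t-test needs 99.08 per arm. The article's 100 therefore reproduces, with power 0.804. A one-sided test would need 78, so the calculation was two-sided. It contains no allowance for clustering.

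**2. Assumptions.** The article lists eight services, so 8 monitors means one per service. The range taken is 8 to 32 monitors (k) and a monitor ICC (r) of 0.01 to 0.10. These are assumptions. With n = 100 TCApp patients analysed, caseload m = 100/k runs from 12.5 down to 3.125. Total SD is 1.

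**3. Monitor clustering alone.** Only the TCApp arm carries the design effect DE = 1 + (m − 1)r, so Var(difference) = (1 + DE)/n.

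For k = 8 and r = 0.05:
- DE = 1 + 11.5 × 0.05 = 1.575.
- Var = 2.575/100 = 0.02575, so SE = 0.1605.
- The SE under independence is √(2/100) = 0.1414, a ratio of 1.135.
- Type I error of the test that ignores nesting: 2 × [1 − Φ(1.96/1.135)] = 0.084.
- Power of a valid test: Φ(0.40/0.1605 − 1.96) = 0.703, or 0.655 with Satterthwaite df of 18.

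| Monitors | ICC | SE ratio, true/naive | Naive type I error | Valid power (Satterthwaite) |
|---|---|---|---|---|
| 8 | 0.01 | 1.028 | 0.057 | 0.751 |
| 8 | 0.05 | 1.135 | 0.084 | 0.655 |
| 8 | 0.10 | 1.255 | 0.118 | 0.558 |
| 16 | 0.01 | 1.013 | 0.053 | 0.782 |
| 16 | 0.05 | 1.064 | 0.065 | 0.739 |
| 16 | 0.10 | 1.124 | 0.081 | 0.689 |
| 32 | 0.01 | 1.005 | 0.051 | 0.795 |
| 32 | 0.05 | 1.026 | 0.056 | 0.778 |
| 32 | 0.10 | 1.052 | 0.062 | 0.758 |

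**4. The opposing effect of stratification.** Randomisation within ED unit balances a centre effect that both arms share. An analysis that ignores unit keeps that variance in its standard error, which makes it too large. With centre ICC c, Var = [2(1 − c) + (m − 1)r]/n. The two effects balance when r = 2c/(m − 1).

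With an assumed c = 0.05, break-even is r = 0.10/11.5 = 0.009 for 8 monitors and 0.10/5.25 = 0.019 for 16. Naive type I error is then:

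| Monitors | r = 0 | r = 0.01 | r = 0.05 |
|---|---|---|---|
| 8 | 0.044 | 0.051 | 0.078 |
| 16 | 0.044 | 0.047 | 0.059 |

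For 32 monitors and r = 0.05, Var = (1.9 + 2.125 × 0.05)/100 = 0.02006, against 0.02 under independence: no practical error.

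**5. What a correct model delivers with 8 monitors.** With one monitor per unit, a model with ED unit and a monitor effect in the TCApp arm reduces to a comparison of 8 within-unit differences, so df = 7 and the critical t is 2.365. For c = r = 0.05, Var = (1.9 + 0.575)/100 = 0.02475, SE = 0.1573 and the non-centrality is 0.40/0.1573 = 2.543. The noncentral t gives power of about 0.59. For r = 0.01, Var = 0.02015 and power is about 0.68. Simulation of these 8 differences (40,000 replicates) gives type I error of about 5% in both cases.

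**The case against.** **The harm rests on assumed inputs.** This stands. The article gives no ICC and no number of monitors, and nowhere says that monitors are few. With 32 monitors, or a monitor ICC near 0.01 and a shared centre effect, little or nothing is lost.

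**Stratification works the other way.** This stands in direction. A reader might infer that the standard error is certainly too small and the false-positive rate certainly above 5%. The documents do not support that: at low monitor ICC the naive test can be slightly conservative. The offset does not remove the problem with about 8 monitors at ICC 0.05, where type I error is still about 8%.

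**The model is not stated to assume independence.** This stands in part. The article lists only the independent variables of a mixed model, and a condensed article commonly leaves random effects to a fuller document. A reader might infer that the model excludes clinician clustering; the text does not say so. What the article does state is a sample size built on independence, and subgroup analysis as its response to differences between centres.

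**Controls also have clinicians.** This is true. They are treated in the same units, and Table 1 has the clinician responsible for online monitoring reporting suicide risk and healthcare use at T0, T1 and T2 without restriction to one arm. It would be too strong to say that controls sit under no clinician. But clinician effects common to both arms largely cancel, whereas the effect of delivering the online monitoring does not.

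**Conclusion.** The point holds conditionally. The documents establish partial nesting: one monitor per patient, monitoring in the TCApp arm only before T2, and both arms within the same ED units. They also establish that the sample size makes no allowance for it and that the stated model names neither a monitor nor an ED-unit term.

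The documents do not establish the size, or at low ICC even the direction, of the resulting error. Under the assumed inputs, naive type I error is about 8% with 8 monitors and a monitor ICC of 0.05, with or without a centre ICC of 0.05. With 16 monitors it is about 6%. With 32 monitors, or an ICC near 0.01 plus a shared centre effect, it is about 5% or a little below. The stated 80% power is therefore a figure under independence, and its relevance depends mainly on how many monitors there are.

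**What to change.** 1. **Record the monitoring clinician's ID** for each TCApp patient. These clinicians already complete questionnaires and interviews, so the study knows who they are.
2. **Model.** Include ED unit, the randomisation stratum, in the EDE-Q model and the other patient-outcome models. Add a random effect for monitoring clinician in the TCApp arm only, with Kenward-Roger or Satterthwaite degrees of freedom. Where a unit has one monitor, this is equivalent to a unit-by-treatment random effect. Take the estimate and confidence interval from this model.
3. **Power.** In the sample size section, state power over the planned number of monitors and an ICC range such as 0.01 to 0.10, instead of 80% under independence.

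ED unit must be in the model. A monitor effect alone, with each control as a singleton, would attribute the shared unit effect to the TCApp arm. In simulation with 8 units, one monitor each, centre ICC 0.05 and no monitor effect, that test has type I error of 2.6% and power of 69%, against 82% for the plain t-test.

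**Cost.** One ID variable and revised analysis wording; no added patients. The interval will be wider and the stated power less favourable. With only about 8 monitors the variance component is imprecise and power falls appreciably, to roughly 0.59 at monitor and centre ICCs of 0.05.
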